### Anthropology, Health economics and Mathematical modelling

Prior to starting the trial and during the intervention, socio-cultural factors in relation to the intervention’s effectiveness, including its local acceptability, will be assessed using ethnographic qualitative methods (participant observation, in-depth interviews and group discussions). Before the mass vaccination campaign, potential bottlenecks for the intervention will be assessed, and recommendations will be made to improve its implementation. This will help fine-tune the implementation of the intervention to local realities in addition to engaging stakeholders to ensure participation and retention. During this phase, we will involve community members and stakeholders in the process of developing/adapting the mass vaccination implementation strategy to increase coverage of the intervention. A comprehensive stakeholder assessment will be carried out at the beginning of the project, aiming to identify formal and informal groups and organisations active in the communities.

A health economics study on the cost-effectiveness of the intervention will be carried out. A cross-sectional survey will be carried out at the beginning of the project in both study arms to estimate the cost of seeking care among households and the costs supported by the health facility. Cost of mass vaccination will be collected for each round. Questionnaires will be administered to collect all the data at household and health facility levels.

Mathematical modelling will be used to generalise the findings from the trial to provide direct support for policy decision-making. This will build on extensions of an existing modelling framework that has been used to support decision-making for the RTS,S vaccine [17, 18].

### Study outcomes

The primary endpoint is the prevalence of malaria infection measured by molecular methods (qPCR) in all age groups as determined by a cross-sectional survey at the peak of the first transmission season, i.e. in November 2024, following the primo-vaccination. Secondary endpoints are as follows: [1] occurrence of AEs; [2] incidence of malaria infection in all age groups during the transmission season following primo-vaccination; [3] incidence of clinical malaria in all age groups following primo-vaccination; [4] prevalence of malaria infection by molecular methods in all age groups at peak transmission following the booster dose; [5] incidence of malaria infection in all age groups during the transmission season following the booster dose; [6] incidence of clinical malaria in all age groups following the booster dose; [7] coverage of the intervention and community acceptability; [8] cost of vaccine administration, both for the primo-vaccination and the booster dose; [9] incremental cost-effectiveness. Exploratory outcomes are prevalence of serological markers (AMA-1, MSP-1, GLURP, GexP, RH2030 and Etramp5.Ag1) at peak transmission after the mass vaccination campaign with 3 monthly doses and the booster dose.

### Sample size and statistical analysis

The primary analysis will be a comparison of the cluster level malaria prevalence rates following the primo-vaccination (3 doses) between the two arms. Arms will initially be compared by a two-samples one-sided *t*-test (2.5%), and, to be conservative, the variance between prevalence in each arm will be assumed unequal (Welch approximation). The intra-cluster correlation coefficient (ICC) is estimated at 0.17 for Burkina Faso [19] and at 0.10 for The Gambia [15]. The malaria prevalence in the control arm is assumed to be 40% in Burkina Faso and 13.5% in The Gambia [15]. Assuming malaria prevalence in the intervention arm will decrease by about 45% compared to the control arm, 12 cluster per arm in Burkina Faso and 15 cluster per arm in The Gambia with 100 individuals per cluster would be needed to detect such a reduction between study arms with 80% power and a 5% significance level. The sample size has been estimated for each country separately as the impact of the intervention may differ between countries (Fig. 2).

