**Fig. 3 Fig3:**
[figure not shown]
Reduction of incidence rate detected by sample size at 80% power

The primary outcome, prevalence of malaria infection, defined as the proportion of sampled residents carrying the parasite (*P. falciparum*) detectable by varATS PCR, will be compared between study arms using random effects logistic regression (with random effect on village) adjusting for study month, age group (< 5, 5–15 and > 15), ITN use and baseline malaria prevalence by village.

For secondary outcomes, incidence of clinical malaria will be estimated by recording all clinical cases from study villages (both intervention and control) attending the local health facilities or diagnosed by study nurses based in study villages (passive case detection). Incidence will be compared between arms using random effects Poisson regression—a random effect for study village will be included for the clustering. Incidence of malaria infection will be estimated by the number of first or only infections over person-months of follow-up. Intervention coverage will be measured by dividing the number of individuals having completed the vaccination schedule (3 monthly doses) by the number of individuals eligible for vaccination. In addition, coverage of at least one vaccine dose will be estimated. Coverage will be calculated for each vaccination round and intervention year, while community acceptability will be assessed qualitatively in both the intervention and control arms. Vaccination costs and cost-effectiveness will be estimated by the annual costs of the vaccination campaign and the vaccine delivery cost per vaccinated individual. The cost-effectiveness will be estimated for the intervention (mass vaccination campaign) compared to the status quo (no mass vaccination campaign).

The exploratory outcome, the prevalence of serological markers (AMA-1, MSP-1, GLURP, GexP, RH2030 and Etramp5.Ag1), will be compared between arms using random effects logistic regression (with random effect on village).

Missing data percentages will be reported; available case analysis will be performed unless there is a higher missing data rate (> 15%) in which case we will consider using multiple imputation for the analyses. Primary analysis will be based on intention-to-treat approach; however, we will explore a treatment effect separately for those receiving the full dose as per the protocol and those receiving partial doses in sensitivity analyses.

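### The protocol gives the primary outcome two different analyses, an unadjusted village-level t-test and an adjusted random-effects logistic model, and does not say which decides

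*Protocol article*

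**What the plan says.** Both statements are in the protocol article under *Sample size and statistical analysis*.

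- The opening paragraph says: "The primary analysis will be a comparison of the cluster level malaria prevalence rates following the primo-vaccination (3 doses) between the two arms". It goes on: "Arms will initially be compared by a two-samples one-sided *t*-test (2.5" (per cent), with unequal variances. The sample size follows in the same paragraph, "with 80% power and a 5% significance level".
- After Fig. 3, the primary outcome (infection by varATS PCR) "will be compared between study arms using random effects logistic regression (with random effect on village) adjusting for study month, age group", and also for "ITN use and baseline malaria prevalence by village".

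Two other sections bear on this. *Village selection and Informed consent* restricts randomisation so that mean baseline prevalence in the two arms lies within ±10%. *Randomisation and blinding* adds ITN coverage and distance from health facilities as examples of balancing factors. The t-test adjusts for none of these, and the logistic model omits distance.

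**The concern.** These are two tests of two effect measures: a difference in mean village prevalence, and an odds ratio conditional on village and covariates. The word *initially* before the t-test gives an order but no hierarchy. The later statement that the primary analysis follows intention to treat fixes the population and not the model. If one analysis is significant and the other is not, the protocol does not say whether the trial has succeeded. In an open-label trial that should be settled in writing before the outcome data are seen.

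The two candidates also err in opposite directions. An unadjusted test after restricted randomisation is too cautious. A mixed model with 24 or 30 villages tends to be too liberal unless its inference is corrected.

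**Working it through.** **Inputs from the protocol.** "12 cluster per arm in Burkina Faso and 15 cluster per arm in The Gambia with 100 individuals per cluster". The ICC "is estimated at 0.17 for Burkina Faso [19] and at 0.10 for The Gambia [15". Control prevalence is 40% and 13.5%, and the reduction is 45%, so intervention prevalence is 0.55 × 40% = 22% and 0.55 × 13.5% = 7.425%.

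**Assumptions not in the protocol.** Village prevalences are logit-normal with mean and ICC matched to the plan (random-effect SD 1.00 and 0.95). Baseline and outcome village effects correlate 0.6. The ±10% limit is relative. Individual-level covariates are not simulated.

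**1. The plan's own figure.** The 80% power is stated alongside the Welch test. The design effect is 1 + 99 × ICC, which is 17.83 and 10.90.
- Burkina Faso: SE = √[(0.24 + 0.1716) × 17.83 / 1200] = 0.0782, and 0.18 / 0.0782 = 2.30.
- The Gambia: SE = √[(0.116775 + 0.068737) × 10.90 / 1500] = 0.0367, and 0.06075 / 0.0367 = 1.65.

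At one-sided 2.5% the noncentral-t power is about 59% and 36%; simulation gives 59% and 37%. The 80% is not reproduced. That is a separate matter, noted here because it is the only operating characteristic the protocol attaches to either analysis.

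**2. Do the two analyses agree?** With the 45% reduction true, one set of runs (800 trials per country, logistic model by maximum likelihood with Wald z and one baseline covariate) gave these rejection rates at one-sided 2.5%:

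| | Welch | Logistic | Opposite verdicts |
|---|---|---|---|
| Burkina Faso | 64% | 84% | about 24% |
| The Gambia | 37% | 62.5% | about 27% |

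A second simulation put disagreement at about 22-30%. Part of the model's higher rejection rate comes from baseline adjustment, and part from its inflated error rate (step 4).

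**3. Error of the unadjusted Welch test.** Under simple randomisation the two-sided error is 4.9% (Burkina Faso) and 4.6% (The Gambia). The trial will not use simple randomisation. With the ±10% restriction, separate simulations gave 1.5-2.1%. An approximate check: balancing a covariate correlated 0.6 with outcome leaves 1 − 0.6² = 0.64 of the variance of the arm difference, so its SD shrinks by 0.8. The effective critical value in Burkina Faso becomes 2.07 / 0.8 = 2.59 on 22 degrees of freedom, a two-sided tail of about 1.7%. For The Gambia it is 2.05 / 0.8 = 2.56 on 28, about 1.6%.

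Under the same restriction a baseline-adjusted cluster-level test holds 4.7-5.0% error. It raises power from about 62% to 77% in Burkina Faso and from 38% to 54% in The Gambia.

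**4. Error of the logistic model**, two-sided nominal 5%, fitted within country, unrestricted allocation:

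| Village-level covariates | Burkina Faso, Wald z | The Gambia, Wald z | Likelihood ratio (both countries) | t degrees of freedom (both countries) |
|---|---|---|---|---|
| none | 6.6-7.3% | 6.6-7.0% | 5.5-6.3% | 5.0-6.0% |
| baseline prevalence | 7.9-8.0% | 6.8-6.9% | 6.1-7.0% | 5.5-6.4% |
| two | 9.2% | 8.2% | 7.4-7.8% | 7.0-7.2% |
| three | 9.7% | 8.1% | 7.4-8.4% | 7.0-7.5% |

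Monte Carlo error is about 0.3 points. With the ±10% restriction and baseline prevalence in the model, Wald z gave 7.5% and 6.9%, and t degrees of freedom 5.9% and 6.0%. Pooled over both countries (54 villages) with unrestricted allocation, Wald z gave 6.5%.

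**5. Effect measure.** Solving for the conditional odds ratio that lowers marginal prevalence by 45% gives about 0.36 in Burkina Faso and 0.48 in The Gambia. These are the planned reduction on another scale.

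**The case against.** The strongest reply is that only one comparison is called the primary analysis, only that one carries an alpha, and the sample size is introduced under it. *Initially* would then mean unadjusted first and adjusted second, both prespecified. This is a natural reading. But the later paragraph presents the logistic model as how the primary outcome will be compared, without calling it secondary or supportive, so the text does not settle the matter.

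Three further objections stand and limit the point.

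- A reader might infer that the logistic model simply rejects a true null 8-9% of the time. The protocol does not support that. It does not state how the p-value is obtained, which an analysis plan may fix, and it does not say that the model is fitted per country. Baseline prevalence is the only covariate that is certainly village-level. Age group is individual, ITN use most naturally so, and a November survey leaves little variation in study month.
- A reader might infer that the stated one-sided 2.5% is not controlled. That level is attached only to the Welch test, which holds it and, under restriction, falls below it.
- A reader might infer that the headline will be an inflated odds ratio. The article names no reported effect measure, so this is conjecture. That a conditional odds ratio differs from a prevalence ratio is a property of the model and not an error in the plan.

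Finally, the two-stage method is one valid remedy among several. Naming the deciding analysis is what is strictly required.

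**Conclusion.** The point holds as a conflict between two stated analyses of one primary outcome, with no rule for which decides. This is not detail left to an analysis plan, because the article states both. The consequence is material: opposite verdicts in roughly 22-30% of trials under the planned effect. Each candidate as written has a weakness. The unadjusted t-test is conservative, at about 2% two-sided, and gives up power. The logistic model runs at about 7-8%, possibly 8-10% with two or three village-level covariates, but only if fitted within country with uncorrected Wald z.

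The disagreement and restricted-error figures rest on the assumed 0.6 correlation. The restricted figures also depend on reading ±10% as relative. A weaker correlation would make the t-test less conservative and adjustment less valuable. The need to name one analysis depends on none of these assumptions.

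**What to change.** Name one deciding analysis per country, state its sidedness and level, and label the other supportive.

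The preferred choice is a cluster-level comparison adjusted for baseline prevalence and the other balancing factors. One form is the two-stage method. Stage one is a logistic regression without arm on age group and the balanced village factors. Stage two is a Welch t-test on village observed-to-expected ratios, giving an adjusted prevalence ratio with its confidence interval.

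If the logistic model is to decide instead, specify a small-sample or permutation-based p-value that respects the restricted allocation, and report a standardised prevalence ratio or difference beside the odds ratio. Degrees-of-freedom correction alone reduces the excess but does not always remove it. If an existing analysis plan already fixes the hierarchy, cite it and align the protocol wording.

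The cost is wording in the protocol and analysis plan and a little more analysis code. No change to data collection is needed.

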**Discussion:**

This is the first trial on seasonal mass vaccination aiming at reducing malaria transmission. Strengths of the study include its design as an adequately powered cluster-randomised trial and the inclusion of study sites with differing transmission intensity which will also provide safety and efficacy data for different age groups. Key challenges remain vaccine hesitancy and vaccination coverage. If successful, R21 seasonal mass vaccination will be an innovative intervention to accelerate malaria elimination efforts and reach the goal set in the Global Technical Strategy for malaria 2016–2030.

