With limited resources, along with a growing gap between available funding and resources needed to meet the WHO’s Global Technical Strategy (GTS) targets, it has become increasingly important to evaluate the cost and the cost-effectiveness of new interventions to ensure that scarce funding is allocated efficiently. Therefore, we will also estimate the cost and cost-effectiveness of seasonal mass vaccination with R21 in each study site.

This is the first cluster randomised trial on seasonal mass vaccination to reduce malaria transmission. Strengths of the study include its design as an adequately powered cluster randomised trial and the inclusion of study sites with differing transmission intensity which will also provide safety and efficacy data for different age groups, i.e. older children and adults, that were not included in the large phase II and III trials implemented to register the vaccine. If mass vaccination with R21 shows a major impact on malaria transmission, it will become a powerful tool to further reduce malaria burden. However, as previously mentioned, potential challenges of mass vaccination include vaccine hesitancy and population movements, which may reduce vaccine coverage to levels where no or little effect will be achieved.

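### The stated 80% power in each country does not follow from the printed inputs, which give about 59% in Burkina Faso and 36% in The Gambia; the trial's actual power is uncertain

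*Protocol article*

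**What the plan says.** The primary endpoint is fixed in Study outcomes: "The primary endpoint is the prevalence of malaria infection measured by molecular methods (qPCR) in all age groups", from the November 2024 survey. The sizing paragraph in Sample size and statistical analysis compares village-level prevalences by a two-sample t-test at one-sided 2.5%, with unequal variances (Welch). On clustering: "The intra-cluster correlation coefficient (ICC) is estimated at 0.17 for Burkina Faso [19] and at 0.10 for The Gambia [15". On the control arm: "The malaria prevalence in the control arm is assumed to be 40% in Burkina Faso and 13.5% in The Gambia". The target is a relative reduction of about 45%. With 12 and 15 villages per arm, "with 100 individuals per cluster would be needed to detect such a reduction between study arms with 80% power and a 5% significance level". The paragraph adds that each country was sized on its own because the effect may differ between them.

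Two other parts of the design bear on power but do not appear in the sizing. Village selection and Informed consent admits only villages with baseline prevalence of at least 10% (The Gambia) or 30% (Burkina Faso). Later in Sample size and statistical analysis, the regression for the primary outcome adjusts for each village's baseline prevalence.

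The Abstract counts as a strength "its design as an adequately powered cluster-randomised trial", and the Discussion repeats it: "Strengths of the study include its design as an adequately powered cluster randomised trial".

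**The concern.** With ICCs of 0.17 and 0.10 and 100 people per village, the design effects are 1 + 99 × 0.17 = 17.83 and 1 + 99 × 0.10 = 10.9. The 1,200 and 1,500 people per arm then carry the information of about 67 and 138 independent people. That is little for detecting 40% against 22%, and very little for 13.5% against 7.4%.

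At stake is how a non-significant result in one country would be read. Each country was sized separately, and the article says twice that the trial is adequately powered. A reader who trusts 80% would give a null result more weight as evidence against a 45% reduction than the printed inputs support, above all in The Gambia.

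**Working it through.** **Inputs.** All come from the sizing paragraph: control prevalence p1 = 0.40 and 0.135; p2 = 0.55 × p1 = 0.22 and 0.07425; ICC 0.17 and 0.10, first read on the proportion scale (an assumption, since no scale is given); m = 100; c = 12 and 15 villages per arm; one-sided 2.5%. A two-sided 5% level has the same critical value, so the two alpha statements agree.

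**Formulas.** Variance of a village prevalence: V = p(1−p)[1 + (m−1)ICC]/m. Standard error of the difference: √((V1+V2)/c). Power: noncentral t with Welch degrees of freedom.

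| | Burkina Faso | The Gambia |
|---|---|---|
| Difference p1 − p2 | 0.18 | 0.06075 |
| V, control | 0.0428 | 0.01273 |
| V, intervention | 0.0306 | 0.00749 |
| Standard error | 0.0782 | 0.0367 |
| Noncentrality | 2.30 | 1.65 |
| Welch df | 21.4 | 26.2 |
| **Power** | **59.4%** | **35.7%** |

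A beta-binomial simulation of the same test (40,000 trials per country) gives 58.4% and 36.6%; the normal approximation gives 63.4% and 38.0%. With unlimited people per village, power is still only 61% and 38%, so the limit is the number of villages.

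**Turned round, on the same reading.**
- Reduction detectable at 80% power: about 56% and 72%.
- Villages per arm for 80% power at 45%: 19 and 45.
- ICC that would give 80%: about 0.10 and 0.026.

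**Attempts to reach the plan's 80%.**

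| Reading | Burkina Faso | The Gambia |
|---|---|---|
| Constant between-village CV, k = √(ICC(1−p1)/p1) = 0.505 and 0.800 | 70% | 41% |
| ICC on the latent logistic scale, one-sided 2.5% | 65–75% | 68–72% |
| Proportion-scale ICC, one-sided 5% | 72% | 49% |
| Latent-scale ICC, one-sided 5% | 76–85% | 79–82% |
| Both countries pooled by inverse variance | about 81% (joint) | |

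For the latent reading the village variance is ICC × (π²/3)/(1−ICC), that is 0.674 and 0.366. The range covers taking the prevalences as population-average or as those of a typical village. No reading at the stated alpha reaches 80% in both countries. The last two rows come close, but one uses an alpha other than the stated one and the other contradicts the separate sizing.

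**What the sizing leaves out.**
- *Baseline adjustment.* If it removes a share R of between-village variance, V becomes p(1−p)[(1−R)ICC + (1−ICC)/100]. The Welch calculation then gives 80% in Burkina Faso at R = 0.40, and 76% and 81% in The Gambia at R = 0.70 and 0.75. The normal approximation needs slightly less, about 0.35 and just over 0.70.
- *Entry floor.* The Gambian inputs imply a between-village SD of √(0.10 × 0.135 × 0.865) = 0.108, or 11 points around a mean of 13.5%, so many villages would lie below the 10% floor and could not be enrolled. Assume beta-distributed village prevalence, selection on a 100-person survey and a proportional 45% reduction. Power is then 99% and 82% if prevalence persists fully to 2024, 93% and 68% with a between-year correlation of 0.8, and 80% and 49% with 0.4. Another full-persistence set-up gives 96% and 76%. The documents give no between-year correlation, so these figures only illustrate direction and spread.

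**The case against.** The strongest reply is that 59% and 36% do not describe the trial being run. The article gives no ICC scale, and the planned regression is a random-effects logistic model, for which ICCs are often quoted on the latent scale; on that reading the Gambian figure roughly doubles. Enrolled villages must clear a floor that raises mean prevalence and narrows the spread. Baseline prevalence also enters the regression and restricts the randomisation, and the t-test is only the initial comparison. The target is about 45%, and the Discussion cites modelled reductions of 70–80%, which would be easier to detect. Fig. 2, the power curve, was not available for this check, so the method behind the 80% cannot be traced.

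Most of this stands against the exact numbers. It does not rescue the printed statement. The latent reading stays below 80% at the stated alpha, where 80% needs a reduction of about 48–52% in Burkina Faso and 49–50% in The Gambia. The floor and the adjustment are not invoked in the sizing, and the size of their gain rests on persistence that the documents do not quantify. A larger true effect is a different claim from the one made for 45%.

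A reader might infer that a real 45% reduction in The Gambia would be missed about two times in three. That follows only if the proportion-scale reading applies and neither the floor nor the adjustment helps, and the documents establish neither condition. A reader might also count the omitted floor as a further inflation of the stated power; its likely effect is the opposite.

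**Conclusion.** The claim of 80% power per country is wrong as written, because it does not follow from the inputs beside it. On those inputs and the stated test, power is about 59% in Burkina Faso and 36% in The Gambia if the ICCs are on the proportion scale. Under the other readings at the stated alpha it is 65–75% and 41–72%.

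It would be tempting to conclude that the trial is underpowered or needs more villages. The documents do not support that. Once the entry floor and baseline adjustment are allowed for, Burkina Faso may well reach 80%. The Gambia is more uncertain: it needs about three quarters of between-village variance explained on the proportion-scale reading, and the floor scenarios run from 49% to 82%. What is established is an unsupported headline figure for the primary endpoint, and two descriptions of the trial as adequately powered that rest on it.

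**What to change.** 1. State the scale of the two ICCs and whether the ICC or the coefficient of variation is held constant between arms.
2. Recompute power separately for each country, using the mean prevalence and between-village variance of the selected villages in the baseline survey. Do this for the Welch test as stated and again with baseline adjustment, giving the assumed correlation between baseline and November 2024 prevalence and a range around it.
3. Report, per country, the power for a 45% reduction and the reduction detectable at 80% power.
4. Until that is done, withdraw or qualify the 80% in Sample size and statistical analysis and the adequately-powered wording in the Abstract and Discussion. If 59% and 36% are printed meanwhile, label them as the power on the printed inputs with a proportion-scale ICC, not as the power of the trial.

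The cost is a recalculation from data the trial already collects, plus a few sentences. It uses baseline data only, so it does not touch the outcome comparison or its error rate. No extra villages or procedures are needed. The downside is that the stated power may become less favourable, especially for The Gambia.
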